### **7.3 Populations for analysis**

The main analysis will include the data of all participants.

### **7.4 Timing of analysis**

The study data will not be analysed until data collection has been completed in all study centers. No interim analyses will be carried out.

### **7.5 Sample size discussion and power analysis**

Due to the study design as a feasibility study, the primary endpoint for modules 1-3 is the rate of acceptance of the respective surveillance protocol, defined as the proportion of children and childcare workers with successful participation in sample collection (mid-turbinate swab or saliva sample) among all children and childcare workers in the daycare centre. Parent/child groups and childcare workers who do not consent to participation in the study will be included in the calculations as “non-successful” participants. Each study participant will be classed as “successful” with respect to sampling if at least 60% of all scheduled samples were collected successfully. All persons with a positive serological test for SARS-CoV-2 will be classed as “successful” with regard to the primary endpoint as no further sample collection (mid-turbinate swabs or saliva samples) is to be carried out in these cases according to the surveillance protocol.

As the maximum achievable sample size will depend on the number of children and number of childcare workers per centre, it is only possible to state a minimum sample size per module. The estimates of precision will be based on this minimum sample size. If the sample size is greater than expected, the width of the precision estimate will be reduced, allowing a more precise estimation.

The inclusion criteria result in the following minimum sample sizes (number of children and childcare workers) per module:

Module 1 (intensive monitoring / mid-turbinate swabs): 105

Module 2 (extensive monitoring / mid-turbinate swabs): 105

Module 3 (intensive monitoring / saliva samples): 185

Module 4: 275

We assume that the rate of acceptance will depend on the frequency of sampling and the type of sample collection. Based on this assumption, we expect a lower rate of acceptance in module 1 (mid-turbinate swabs twice a week) than in module 2 or 3. We therefore assume the following rates of acceptance:

Module 1 (intensive monitoring / mid-turbinate swabs): 30%

Module 2 (extensive monitoring / mid-turbinate swabs): 37.5%

Module 3 (intensive monitoring / saliva samples): 37.5%

Reasoning for sample size in module 1 (intensive monitoring / mid-turbinate swabs):

A minimum number of 100 children and 5 childcare workers is sufficient to estimate a rate of acceptance of 30% with a precision (half the width of the 95%-CI using the Wilson score method) of max. 9.1%.

Reasoning for sample size in module 2 (extensive monitoring / mid-turbinate swabs):

A minimum number of 100 children and 5 childcare workers is sufficient to estimate a rate of acceptance of 37.5% with a precision (half the width of the 95%-CI using Wilson score method) of max. 8.7%.

Reasoning for sample size in module 3 (intensive monitoring / saliva samples):

A minimum number of 175 children and 10 childcare workers is sufficient to estimate a rate of acceptance of 37.5% with a precision (half the width of the 95%-CI using the Wilson score method) of max. 6.9%.

Module 4:

The primary endpoint for module 4 is the proportion of cases with successful sample collection (i.e. completion of sample collection and diagnostic analysis – or receipt of test result in the case of external testing – within 72h after first telephone contact with hotline) among all cases relevant for sample collection. Testing will be carried out for all symptomatic parents, symptomatic children or childcare workers and further symptomatic household members after obtaining informed consent. The potential number of tests recommended will depend on the number of children and childcare workers in the module, the household size per family and the

proportion with acute respiratory illness (ARI). The (ARI)-physician consultation incidence in Germany varies between 400 and 2,500 per 100,000 inhabitants per week . We assume that the proportion with ARI in our study will correspond to the ARI physician consultation incidence at times of high prevalence as we reckon with a large number of unrecorded cases and the research study will be carried out during a period of high prevalence. We furthermore assume that module 4 will include 250 parent/child groups plus 25 childcare workers. According to data of the German Federal Statistical Office for 2018, the average family size is 3.5 persons . Based on this data, the following expected number of recommended tests is derived:

number of recommended tests = household size \* (children+childcare workers) \* proportion with acute respiratory illness per week \* observation period in weeks

$$=3.5*275*0.025*12= 279$$

We assume that 70% of all sample collections planned will be successful. A number of 279 recommended tests will be sufficient to estimate a 70% proportion of successful sample collections with a precision (half the width of the 95%-CI using the Wilson score method) of 5.4%.

Sample size for the qualitative interviews:

For the interviews with parents/guardians, we expect a number of approximately 10 participants per study arm, who shall be recruited from all participating daycare centers (module 1/2, module 3, module 4: 25-30). Overall, we expect 50-60 interviews to be carried out with parents/guardians (counting interviews at the beginning and at the intervention). For the interviews with childcare workers, candidates will be recruited from all participating daycare centers and we expect approximately 20 participants for the first round of interviews and 20 for the final interviews. The total number of interviews is therefore expected to lie in the range of 80-100.

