#### **4.3.3 Serology**

In order to carry out serological testing for SARS-CoV-2 antibodies, finger-prick testing to obtain a few drops of blood from all participants (children, childcare workers) will be used once at the beginning of the study programme and once more at the end of the study. The finger-prick tests will be carried out by trained staff supervised by pediatricians.

Venous blood samples will be taken only in the event of a positive or borderline result in the finger-prick test and only if explicit informed consent for venous blood sampling was obtained (cf. 4.2).

The serological tests will be carried out on site using a point-of-care test and at the Institute of Hygiene and Microbiology and/or the Institute of Virology at the University of Würzburg.

Any sample material remaining after carrying out the tests will be stored for a period of 10 years. Antibody tests for the detection of SARS-CoV-2 antibodies are at present being refined at a high rate of innovation. Storing any remaining sample material will enable renewed testing using more refined techniques in the future.

All study participants (parents/guardians in the case of children) will be notified of the serological test results. No respiratory sample collection and no further blood sampling at the end of the study will be performed in participating children and childcare workers tested positive in the initial serological test.

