### **6.4.3 Blood tests**

Blood samples will be taken using finger-prick testing with single-use safety lancets. After disinfecting and pricking the fingertip, a few drops of blood will be drawn into a capillary tube for performing the point of care test.

In the event of a positive or borderline result (approximately 1% of test results), parents/guardians will be given the option of additional venous blood sampling (1ml, in accordance with WHO guidelines ), which will be carried out by a physician under the supervision of a pediatrician if written consent is obtained.

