## 7 BIOMETRICAL ASPECTS

### 7.1 Endpoints

#### Primary endpoints for the different surveillance measures

- [Modules 1-3]: Rate of acceptance of the respective surveillance protocol defined as: proportion of children/childcare workers with “successful” participation in sample collection (mid-turbinate swab or saliva sample) among all children and childcare workers in the daycare centre. Parent/child groups and childcare workers who do not consent to participation in the study will be included in the calculations as “non-successful” participants. Each study participant will be classed as “successful” with respect to sample collection if at least 60% of all scheduled samples were collected successfully.

A surveillance protocol will be classed as “successful” if the rate of acceptance exceeds the following level:

≥30% (Module 1: intensive monitoring / mid-turbinate swabs)

≥37.5% (Module 2: extensive monitoring / mid-turbinate swabs)

≥37.5% (Module 3: intensive monitoring / saliva samples)

- [Module 4]:  
Proportion of cases with successful sample collection (i.e. completion of sample collection and diagnostic analysis – or receipt of test result in the case of external testing – within 72h after first telephone contact with hotline) among all cases of sample collection recommended for symptomatic children, symptomatic childcare workers or symptomatic household members of children/childcare workers

The surveillance protocol will be classed as “successful” if the rate of acceptance exceeds the following level:

≥70% (Module 4: symptom-based monitoring)

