#### **Exploratory Analyses regarding effectiveness of the intervention**

- Proportion of all mid-turbinate swabs tested positive for SARS-CoV-2 (PCR)
- Proportion of all saliva samples tested positive for SARS-CoV-2 (PCR)
- Proportion of parents/siblings/others among all persons tested for SARS-CoV-2 (PCR) [Module 4]
- Proportion of absent days due to respiratory symptoms
- Proportion of absent days due to SARS-CoV2 infection of child and/or SARS-Cov-2 infection of a family member/other contact person (quarantine)
- Closures of daycare groups / daycare centers by the health authorities due to positive SARS-CoV-2 results within the research study
- Closures of daycare groups / daycare centers by the health authorities due to other causes
- Proportion of children and childcare workers with positive serological test result (antibodies) before and after the observation period of 12 weeks

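### Section 7.5 counts every seropositive person as a successful sampler, a wider rule than its own reason supports and one absent from the endpoint definition in 7.1

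*Protocol*

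**What the plan says.** The modules 1-3 endpoint in section 7.1 is the proportion of successful samplers "among all children and childcare workers in the daycare centre", with non-consenters counted as failures. A person is successful "if at least 60% of all scheduled samples were collected successfully". Neither section 7.1 nor the synopsis mentions serology in this definition.

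Section 7.5 repeats the definition and adds an exception: "All persons with a positive serological test for SARS-CoV-2 will be classed as" successful. The reason it offers is that the surveillance plan foresees no more swabs or saliva samples for such people.

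Section 4.3.3 schedules a finger-prick test at the start and another at the end, and says of those positive on the initial test: "No respiratory sample collection and no further blood sampling at the end of the study will be performed in participating children and childcare workers". Sections 4.2 and 11.2 take consent to respiratory sampling and to blood sampling separately.

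Section 7.1 also lists, as an exploratory endpoint, "Proportion of children and childcare workers with positive serological test result (antibodies) before and after the observation period of 12 weeks". Section 7.2 reports seroprevalence over time descriptively. Neither section says how initial positives enter the later figure.

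**The concern.** The exception appears only in the sample size section, and its wording is wider than its reason. Persons positive on the initial test have no scheduled respiratory samples, so the 60% criterion is undefined for them and some rule is needed. Two other groups also fall under the literal wording:

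- People who declined respiratory sampling, agreed to give blood and tested positive. They are refusers of the very measure being evaluated, and the same section counts non-consenters as failures.
- People first positive at the end-of-study test. They were due for sampling throughout and have a sampling record that may show refusal.

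Counting either group as successful adds acceptance that nobody showed. The endpoint is compared with a fixed threshold, and section 1.6 makes the subsequent study conditional on at least one programme passing. An analyst working from 7.1 and one working from 7.5 could reach different verdicts on the same data.

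The secondary issue is research question V (section 1.7), on change in seroprevalence. Because initial positives are not bled again, the later proportion depends on a denominator that the text leaves open.

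**Working it through.** The protocol states no figure for the effect of this rule, so there is none to reproduce.

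**Inputs.** Minimum n is 105, 105 and 185 for modules 1, 2 and 3, and the assumed rates of 30%, 37.5% and 37.5% equal the success thresholds (section 7.5). Section 6.4.3 gives the share of positive finger-prick tests: "In the event of a positive or borderline result (approximately 1% of test results"). That figure includes borderline results and refers to tests, not to everyone in the centre. Let s be the share of persons in the denominator with any positive serology, and a the acceptance among the others. I take s = 1%; 2% and 5% are assumptions that show the range.

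**Size of the shift.** Counted rate = s + (1−s)a. Against removing these persons from numerator and denominator the excess is s(1−a). Against counting them as failures it is s.

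| s | Excess over exclusion, a = 30% | Excess over exclusion, a = 37.5% | Excess over failure |
|---|---|---|---|
| 1% | 0.01 × 0.70 = 0.70 points | 0.01 × 0.625 = 0.62 points | 1.0 point |
| 2% (assumed) | 1.40 | 1.25 | 2.0 |
| 5% (assumed) | 3.50 | 3.12 | 5.0 |

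The Wilson 95% half-widths at the assumed rates are 8.6 points (30%, n = 105), 9.1 (37.5%, n = 105) and 6.9 (37.5%, n = 185).

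**Can it change a verdict?** The smallest passing counts are 32/105, 40/105 and 70/185.

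- One literal-rule refuser reclassified as a failure: 31/105 = 29.5%, 39/105 = 37.1%, 69/185 = 37.3%. All three fail.
- Initial positives excluded instead. Module 1, one person: 31/104 = 29.8%, a fail. Module 2, one person: 39/104 = 37.5%, still a pass. Module 3, two persons: 68/183 = 37.2%, a fail.

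How often would counting rather than excluding decide the verdict, if acceptance among the others sat exactly at the threshold? In module 1 with one seropositive, the verdicts differ only when 31 of the other 104 succeed: P(Bin(104, 0.30) = 31) = 8.5%. In module 2 with one, 0%. In module 3 with two, P(Bin(183, 0.375) = 68) = 6.1%. With 5, 5 and 9 seropositives (about 5%, assumed), it is 23.8%, 23.4% and 27.5%.

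**Seroprevalence.** Let b be baseline prevalence and i the 12-week seroconversion among baseline negatives (both assumed). With baseline positives carried forward the end value is b + (1−b)i. Among retested persons only it is i.

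| b | i | Carried forward | Retested only |
|---|---|---|---|
| 1% | 0.5% | 1.5% | 0.5% (apparent fall) |
| 1% | 1% | 1.99% | 1.0% (no change) |
| 1% | 2% | 2.98% | 2.0% (smaller rise) |
| 2% | 3% | 4.94% | 3.0% (smaller rise) |

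The retested-only figure is low by b(1−i) in every row. It falls only when i is below b.

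**The case against.** The strongest reply is that the reason attached to the rule limits it. Sampling stops only for participants positive on the initial test, so a sympathetic reader would not apply the exception to week-12 positives; and since 7.5 classes non-consenters as failures just before, a respiratory refuser should stay a failure. That is probably what was meant. But the rule says all persons, and nothing states which sentence takes precedence. The ambiguity stands, though the documents do not show that refusers will in fact be counted as accepting.

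A second reply is that for consenting initial positives, success is a reasonable choice and exclusion is not clearly better. If a fraction p of them would have complied, the protocol's rule errs by s(1−p) and exclusion by s(p−a) for p above a. At a = 30% the protocol's rule is closer whenever p exceeds (1 + 0.30)/2 = 65%. These people agreed to give blood, so a high p is plausible. This stands, and is why both versions should be shown.

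A third reply is size. The 1% includes borderline results and applies only to those who give blood, so the realistic shift is below 1 point in a study that calls its analyses exploratory. This also stands.

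A reader might infer that the plan makes seroprevalence appear to fall. The text does not support that. The endpoint is not restricted to retested persons, carrying positives forward fits it equally well, and even on the retested-only reading a fall needs seroconversion below baseline prevalence.

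**Conclusion.** The point holds in a limited form. The exception in 7.5 is missing from 7.1 and the synopsis, and its wording reaches beyond its stated reason to respiratory refusers who gave blood and to persons first positive at week 12. The resulting bias is upward only. With 1% of persons seropositive it is 0.6 to 0.7 points against exclusion and about 1 point against failure. It matters when a result lies close to 30% or 37.5%, which is where the planning assumptions put it, or if seropositivity is well above 1%; the larger shifts rest on an assumed 5%. It would be too strong to say that the acceptance results are materially inflated at the protocol's own figure.

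The seroprevalence point is conditional. A retested-only analysis would understate the end value. The protocol does not commit to that analysis, but does not rule it out.

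**What to change.** State one rule, in the same words, in 7.1 and 7.5:

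- Limit the exception to persons positive on the initial serology who had consented to respiratory sampling.
- Classify everyone else by consent and by samples collected. This includes those who declined respiratory sampling and those positive only at week 12.
- Report acceptance twice: with these initial positives counted as successful, and with them removed from numerator and denominator. Name one as primary and the other as the sensitivity analysis.

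For research question V, report baseline seroprevalence, seroconversion among retested baseline negatives, and cumulative seroprevalence with baseline positives carried forward.

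The cost is wording and one extra line in the results table. Sampling, consent and sample size do not change. In the exclusion version the denominator shrinks by about one person in 105, or two in 185, at the 1% figure.

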## **7.2 Data analysis methods**

The primary endpoints will be estimated as 95% confidence intervals using the Wilson score method. Due to the purely exploratory nature of all analyses and the fact that the four modules will be implemented in separate daycare centers, the significance level will not be adjusted for multiple testing and all analysis results will be interpreted with the necessary caution. The significance level will be set to 5% for all analyses. In a first step, descriptive analyses

(frequency (percent), mean (SD) or median (IQR)) will be reported for all endpoints. The analysis of the secondary endpoints drop out rate, initial rate of consent, acceptance of blood sampling (stratified by childcare workers and parents), proportion of positive serological tests and proportion of positive PCR tests will, in a first step, compare all four groups using test procedures such as the Chi-squared-test, ANOVA or the Kruskal Wallis test as appropriate. Subsequently, pairwise comparisons will be carried out using appropriate post-hoc tests. The rate of acceptance will first be compared between all modules 1 to 3 using the chi-squared test. Analysis of the development of the psychosocial factors over time will be stratified by monitoring module and will use tests for repeated measurements such as the McNemar test, Repeated Measurements ANOVA and the Friedman test. In addition, baseline values and the follow-up values after 12 weeks will be compared between modules using appropriate tests such as the chi-squared test and ANOVA or non-parametric tests followed by post-hoc tests. Potential predictors of the rate of acceptance will be analysed (overall for all modules combined and stratified by module) in univariable analyses using the chi-squared test and, if a sufficient sample size is obtained, additionally using multivariable logistic regression. The analysis of costs, the proportion of absent days and data on the closure of daycare groups will be restricted to descriptive methods. The development of seroprevalence data over time will be reported using descriptive methods, possibly including graphical displays. The results of the children interviews will be reported descriptively using frequencies. If possible, an ICC value (intraclass correlation) for the daycare centers will be calculated as a basis for sample size estimation for a future cluster randomised study. All analyses will be performed in SAS, R or SPSS.

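### The precisions in 7.5 and the Wilson intervals in 7.2 for Modules 1-3 carry no between-centre variation, so they are too narrow as statements about a surveillance protocol

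*Protocol*

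**What the plan says.** Section 3.1 of the protocol assigns one centre each to Modules 1 and 2 and one to three centres to Module 3. In 7.1 the acceptance rate for these modules is a proportion "among all children and childcare workers in the daycare centre", with people who do not consent counted as not successful.

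Section 7.2 fixes the interval: "The primary endpoints will be estimated as 95% confidence intervals using the Wilson score method". No centre term is mentioned. An ICC for daycare centres appears only as something to calculate, if possible, for sizing the later study.

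Section 7.5 gives the planned precision from the minimum head counts (105, 105 and 185):

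- Module 1: "A minimum number of 100 children and 5 childcare workers is sufficient to estimate a rate of acceptance of 30" per cent, with a Wilson half-width of at most 9.1 points
- Module 2: "estimate a rate of acceptance of 37.5% with a precision (half the width of the 95%-CI using Wilson score method) of max. 8.7" per cent
- Module 3: "estimate a rate of acceptance of 37.5% with a precision (half the width of the 95%-CI using the Wilson score method) of max. 6.9" per cent

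It adds that a larger sample than expected will narrow the estimate. In 7.1 the label of success is attached to the surveillance protocol. Under 1.6, at least one programme meeting its criterion is the precondition for planning the follow-on study, and up to two programmes then go into a multicentre cluster-randomised trial.

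**The concern.** The interval counts persons as independent, but the statement it supports is about a protocol. Families and staff in one centre share management, premises, the sampling team and local opinion, so acceptance can differ between centres for reasons unrelated to the sampling method. With one centre per module, that variation is absent from the interval and cannot be estimated from the module's own data.

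At stake is how firmly the acceptance figures can be carried forward. A planner who reads 7.5 will take a protocol's acceptance to be known within about 7 to 9 points. As a statement about other daycare centres, that is too optimistic.

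**Working it through.** **Inputs.** From 7.5: p = 0.30, n = 105 (Module 1); p = 0.375, n = 105 (Module 2); p = 0.375, n = 185 (Module 3). From 3.1: k = 1, 1 and 1 to 3 centres. From 7.2: 95% Wilson intervals, z = 1.96. The ICC is not in the protocol; 0.01 and 0.05 are assumed here.

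**Step 1: the plan's own figures.** Wilson half-width = z/(1 + z²/n) × √[p(1−p)/n + z²/(4n²)].

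- Module 1: 1.96/1.0366 × √(0.002000 + 0.000087) = 8.64 points (stated 9.1)
- Module 2: 1.96/1.0366 × √(0.002232 + 0.000087) = 9.11 points (stated 8.7)
- Module 3: 1.96/1.0208 × √(0.001267 + 0.000028) = 6.91 points (stated 6.9)

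Module 3 reproduces, which confirms that persons are treated as independent with no centre component. Modules 1 and 2 do not reproduce. The stated 9.1 is the Module 2 value. The stated 8.7 is close to the Module 1 value: 30% of 105 is 31.5, and 32 successes out of 105 give 8.68. The two therefore look interchanged. A continuity-corrected Wilson interval gives 9.10 for Module 1 but 9.56 and 7.17 for Modules 2 and 3, so it does not explain all three figures.

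**Step 2: add between-centre variation.** Keep the Wilson formula and replace n by n/DE, with DE = 1 + (m − 1) × ICC and m = n/k. For Module 1 at ICC 0.01: DE = 1 + 104 × 0.01 = 2.04, effective n = 105/2.04 = 51.5, half-width 12.2 points.

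| Module | Centres | ICC 0 | ICC 0.01 (effective n) | ICC 0.05 (effective n) |
|---|---|---|---|---|
| 1 | 1 | 8.6 | 12.2 (51.5) | 20.0 (16.9) |
| 2 | 1 | 9.1 | 12.8 (51.5) | 20.9 (16.9) |
| 3 | 1 | 6.9 | 11.4 (65.1) | 20.4 (18.1) |
| 3 | 2 equal | 6.9 | 9.5 (96.6) | 15.6 (33.2) |
| 3 | 3 equal | 6.9 | 8.7 (115.1) | 13.5 (45.9) |

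For scale, the between-centre standard deviation is √[ICC × p(1−p)]: 4.6 to 4.8 points at ICC 0.01 and 10.2 to 10.8 points at ICC 0.05.

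**Step 3: can more persons help?** With one centre, effective n = n/[1 + (n − 1) × ICC], which approaches 1/ICC as n grows: 100 at ICC 0.01 and 20 at ICC 0.05. The Wilson half-width for p = 0.30 at n = 100 is 8.84 points. So even an unlimited number of persons in one centre would not bring Module 1 down to the 8.64 obtained from 105 independent persons.

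**The case against.** The strongest reply is that this is a feasibility study. Section 7.2 calls all analyses purely exploratory, mentions the separate centres and promises cautious interpretation. The endpoint is defined within the centre, so a centre-level reading of the interval is natural. An ICC is planned for the later trial, and none is available now.

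Much of this stands. The size of the effect rests wholly on an assumed ICC, and only its direction is certain. The caution in 7.2, though, is attached to the decision not to adjust for multiple testing. The protocol nowhere says that the intervals hold only for the centres studied, and it words its conclusion at protocol level.

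Three stronger readings are tempting and are not supported:

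- A reader might infer that the success verdict is unsafe because the interval is too narrow. As worded in 7.1, the rule compares the observed rate with 30% or 37.5%; the interval does not enter it, so a wider one changes no verdict.
- A reader might infer that, because everyone in the centre is in the denominator, the interval describes nothing. That goes too far. It can be read as covering chance variation in individual behaviour over the 12 weeks. What is missing is a label saying so.
- A reader might infer that the stated figures would be right if centres did not differ. For Modules 1 and 2 they are not the Wilson values even then.

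**Conclusion.** The point holds as a matter of what the precision figures describe. For Modules 1-3 they are person-level half-widths, conditional on the centre or centres chosen. As precision for a protocol's acceptance they are too narrow for any positive ICC. At an assumed ICC of 0.01, Modules 1 and 2 move from about 9 to about 12 or 13 points; at 0.05 they reach about 20 or 21. Module 3 depends on how many centres are used: about 11 to 20 points with one centre and 9 to 13 with three equal ones.

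These sizes rest on the assumed ICC range, on equal centre sizes in Module 3, and on the effective-n approximation, which is rough where effective n falls below 20. The mismatch in the Module 1 and 2 figures needs no assumption beyond the Wilson formula that 7.5 itself names. Since the decision rule does not use the interval, the consequence is limited to how the results are read and carried into planning.

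**What to change.** In 7.5:

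- Correct the person-level Wilson half-widths to 8.6 (Module 1), 9.1 (Module 2) and 6.9 points (Module 3), and label them as conditional on the centre(s) studied.
- Beside them, give Wilson half-widths with effective n over an openly assumed ICC range. For 0.01 to 0.05: Module 1 about 12 to 20, Module 2 about 13 to 21, Module 3 about 11 to 20 (one centre) or 9 to 13 (three equal centres).
- Qualify the remark that a larger sample improves precision: more persons in the same centre narrow only the within-centre figure.

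In 7.2:

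- State that the Module 1 and 2 intervals hold only for the single centre.
- State that Module 3 results are also shown per centre if more than one is used.
- State that the classification as successful refers to the centre(s) studied.

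The cost is wording and a less favourable stated precision. No extra participants, centres or data are needed.

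### The Wilson precisions stated for Modules 1 and 2 appear to be interchanged; Module 2's 8.7% cannot be reached with 105 people at 37.5%

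*Protocol*

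**What the plan says.** Section 7.2 fixes the method of analysis: "The primary endpoints will be estimated as 95% confidence intervals using the Wilson score method". Section 7.5 then derives minimum sizes from the inclusion criteria and says that the precision estimates rest on those minima.

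For the two swab modules the minima are equal: "Module 1 (intensive monitoring / mid-turbinate swabs): 105" and "Module 2 (extensive monitoring / mid-turbinate swabs): 105". The assumed acceptance rates differ: "Module 1 (intensive monitoring / mid-turbinate swabs): 30" per cent and "Module 2 (extensive monitoring / mid-turbinate swabs): 37.5" per cent.

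The sample-size reasoning for each module follows. For Module 1 the precision is given as "half the width of the 95%-CI using the Wilson score method) of max. 9.1" per cent. For Module 2 the text reads "A minimum number of 100 children and 5 childcare workers is sufficient to estimate a rate of acceptance of 37.5% with a precision", and that precision is "half the width of the 95%-CI using Wilson score method) of max. 8.7" per cent. Section 7.5 also states 6.9% for Module 3 (185 people, 37.5%) and 5.4% for Module 4 (279 recommended tests, 70%).

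**The concern.** For a fixed number of people, the interval for a proportion widens as the proportion moves towards 50%. Modules 1 and 2 share the same number, so Module 2 (37.5%) must have the wider interval. The protocol gives it the narrower one. That order is wrong whatever the rounding.

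The study tests no hypothesis on its primary endpoints. These precision statements are the quantitative argument that 105 people per module are enough. Module 2 is promised a ceiling on its half-width that its own inputs exceed. The reported Wilson intervals will be read against these figures, and the results are meant to inform planning of a later cluster-randomised study.

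**Working it through.** **Inputs (Protocol 7.2 and 7.5).** Two-sided 95% Wilson interval, z = 1.960. Module 1: n = 100 + 5 = 105, p = 0.30. Module 2: n = 105, p = 0.375. Module 3: n = 175 + 10 = 185, p = 0.375. Module 4: n = 279 as printed, p = 0.70.

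**Formula.** Half-width h = [z / (1 + z²/n)] × √[ p(1−p)/n + z²/(4n²) ].

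With n fixed, p enters only through p(1−p), which rises up to p = 0.5. Here 0.30 × 0.70 = 0.2100 and 0.375 × 0.625 = 0.2344, so Module 2 must be wider.

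**Numbers for n = 105.** z²/n = 0.0366 and z²/(4n²) = 0.0000871.

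- Module 1: h = (1.960 / 1.0366) × √(0.0020000 + 0.0000871) = 0.0864, interval 22.1% to 39.3%.
- Module 2: h = (1.960 / 1.0366) × √(0.0022321 + 0.0000871) = 0.0911, interval 28.8% to 47.0%.

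**Reproducing the plan's own figures.** Using the nearest whole number of successes in each module:

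| Module | Count | h at that count | h at the exact rate | Printed |
|---|---|---|---|---|
| 1 | 32/105 | 8.68% | 8.64% | 9.1% |
| 2 | 39/105 | 9.09% | 9.11% | 8.7% |
| 3 | 69/185 | 6.90% | 6.91% | 6.9% |
| 4 | 195/279 | 5.35% | 5.35% | 5.4% |

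Modules 3 and 4 come out as printed. For Module 4 the whole count matters: 5.353% rounds to 5.4%, while exactly 70% gives 5.347%, which rounds to 5.3%. The same convention gives 8.7% for Module 1 and 9.1% for Module 2, the two printed figures in reverse order.

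**Could another method explain the printed pair (9.1 and 8.7)?** At n = 105:

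| Method | Module 1 | Module 2 |
|---|---|---|
| Wilson with continuity correction | 9.10 | 9.57 |
| Wald | 8.77 | 9.26 |
| Clopper-Pearson | 9.14 | 9.62 |
| Rate minus lower Wilson limit | 7.93 | 8.67 |
| Upper Wilson limit minus rate | 9.34 | 9.55 |

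None gives the printed pair. In every row Module 2 is the larger. Changing n does not help either: plain Wilson gives 8.85 and 9.32 at n = 100, 8.60 and 9.06 at n = 106, and 8.45 and 8.90 at n = 110.

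**Size needed for 8.7% at a rate of 37.5%.** h = 8.71% at n = 115 and 8.68% at n = 116, which is 10 to 11 people above the stated minimum.

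**The case against.** The arithmetic is hard to contest; the weight of the point is not.

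- **The minima do not come from these figures.** Section 7.5 says they follow from the inclusion criteria, so correcting the precision changes no number of centres or people. This stands. Even so, the section presents the precision as its reasoning for the sample size, so a wrong figure there is still a wrong justification.
- **The shortfall is slight.** It is about 0.4 points on a half-width of about 9, at the minimum size only, and a larger centre would narrow it. This also stands, but the claim is made for 105 people, and there it fails.
- **Module 1's statement is literally true.** A half-width of 8.64% does lie below 9.1%. Correct: only Module 2's ceiling is false, while Module 1's is merely loose.
- **The cause is inferred.** The document does not show that two numbers were exchanged. True, although one convention fits all four printed figures once they are.
- **The synopsis asks for more than 5 childcare workers.** That implies at least 106 people, but Module 2 is then still 9.06%.

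**Conclusion.** The point holds. With 105 people and a rate of 37.5%, the 95% Wilson half-width is 9.1%, so Module 2's stated maximum of 8.7% is not met; the gap is 9.11 − 8.7 = 0.41 percentage points. Module 1's half-width is 8.6% to 8.7% against a stated maximum of 9.1%, a bound that is too wide by 0.42 to 0.46 points. An interchange of the two figures is the most likely cause, because it is the only change needed for all four modules to reproduce.

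This rests only on the protocol's own sizes, rates, interval method and definition of precision. It is a small error with no effect on the minimum sizes, the success thresholds or the planned analysis. It should be corrected because it misstates the precision of two primary endpoints.

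**What to change.** In section 7.5, change the Module 1 precision to max. 8.7% and the Module 2 precision to max. 9.1%. It would help to add that the values are rounded to the nearest 0.1% and computed at the nearest whole count (32 of 105 and 39 of 105), since that is the convention that fits Modules 3 and 4. The cost is two numbers and at most one short clause.
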